## Methods

### Study Design

The studies are conducted and described according to the CONSORT-eHealth checklist [49], which can be found in Multimedia Appendix 1. The outline of the SF and SF2.0 trials is presented in Figure 1. In both trials, the assessment of outcomes is identical and is completed at baseline (T_0_) after the 3-week intervention (or no intervention) period (postintervention, T_1_), and 4 weeks after T_1_ (follow-up, T_2_). Each family (parents and children) is invited to the laboratory for an individual introductory session. Each family member receives an accelerometer for physical activity assessment and a daily paper-pencil–based diary assessing type, intensity, duration and joint activities as well as food intake (specifically fruit and vegetable intake) during the first assessment week (T_0_, Figure 1). At the end of week 1 (end of T_0_), they fill in a questionnaire (paper-pencil in SF, web-based questionnaire in SF2.0) and return all the materials to the laboratory. The completion of the questionnaire takes about 20 minutes. Both parents and children complete individual daily diaries and questionnaires. The data of the preintervention (baseline) assessment (T_0_) are analyzed and they serve as the basis for the weekly goal set-up in the intervention group during the following intervention period.

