**Figure 2 figure2:**
[figure not shown]
Detailed depiction of the operation principles of the SMARTFAMILY apps.

When starting the intervention, all families of the intervention group are asked to set a collective weekly goal for physical activities, which they want to achieve as a family within 1 week, that is, total steps and total time spent on physical activity per family. In addition, collective family goals are set for activities within the family and healthy eating, ie, the amount of fruit and vegetable intake per family and the number of family meals. It is important to note that every single family member is contributing to the collective family goal through his or her own behavior. In contrast to the set goals related to common recommendations such as 10,000 steps a day or 5 servings of fruits and vegetables per day for individuals, the family sets its own collective goals. In order to facilitate realistic goal-setting at the beginning of the intervention, the family members can rely on the analysis of their individual physical activity level and fruit and vegetable intake assessed during T_0_. The goal-setting process is repeated every week during the intervention period. The only goal-setting instruction given to the participants is the recommendation to set collective family goals for the coming week, which are slightly higher than their current cumulative performance. In SF2.0, an interactive goal-setting coach assists with this decision. This procedure involves usage of behavior change techniques, which will be presented in detail below.

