### Randomization and Blinding

Both trials (SF and SF2.0) are cluster randomized controlled trials with 2 groups: (1) an intervention group receiving the SF or SF2.0 and (2) a nonintervention control group. Recruited families who provide informed consent are allocated to one of the 2 groups prior to recruitment by using a simple randomization procedure for cluster designs [51]. Although the intervention group participants are told about the mHealth nature of the study, control group participants are only told to take part in an epidemiologic assessment of physical activity levels, making it essential to wear the accelerometers 2 times for 1 week and to answer several questions over the course of 10 weeks in order to gain reliable and valid results.

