### Data Analysis

First, the baseline characteristics of the study population are summarized within each cluster randomized group on individual and family levels for all measures to control for group differences. Then, all primary outcome data will be screened for normal distribution by using the Shapiro-Wilk test. Data will be checked for outliers. To further analyze changes in health behavior, mixed-model analysis of covariance with time (T_0_ and T_1_ for device-based physical activity; T_0_, T_1_, and T_2_ for self-reported physical activity and healthy eating) as within-subjects and group (intervention group vs control group) as between-subjects factor will be conducted, with covariates being family health climate, self-efficacy, and intrinsic motivation (Behavioral Regulation in Exercise Questionnaire and Regulation of Eating Behavior Scale) as well as intention in SF2.0. Results of the Mauchly test will be checked for homoscedasticity of data and results will be corrected accordingly (ε>0.75 Huynh-Feldt, ε<0.75 Greenhouse-Geisser). Furthermore, homogeneity of the error variances will be checked, as assessed by Levene test. If this test does not reveal significance, a Box-Cox transformation will be applied to the data. Moreover, Tukey-corrected posthoc tests will be considered for detailed interpretation of results. Main effects will only be considered if the interaction is found to be significant. All analyses will be conducted using SPSS 26 statistical software (IBM Corp).

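### Families are randomised, but the planned time-by-group ANCOVA has no family term, so its group-by-time test is anti-conservative to the extent that members' changes correlate within families

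*Protocol article*

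**What the plan says.** The Randomization and Blinding section states: "Both trials (SF and SF2.0) are cluster randomized controlled trials with 2 groups". What is allocated is the recruited family. Measurement is personal. Under Study Design, "Both parents and children complete individual daily diaries and questionnaires", and each member wears an accelerometer.

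The Data Analysis section then names the model for the primary outcomes: time "as within-subjects and group (intervention group vs control group) as between-subjects factor will be conducted". The covariates are family health climate, self-efficacy and intrinsic motivation, with intention added in SF2.0. The diagnostics follow: "Results of the Mauchly test will be checked for homoscedasticity of data", with Huynh-Feldt or Greenhouse-Geisser correction, and a Levene test. The family level appears once in that section, for the baseline description, where measures are "summarized within each cluster randomized group on individual and family levels for all measures".

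On the intervention itself, Study Design says that "every single family member is contributing to the collective family goal through his or her own behavior".

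**The concern.** In a cluster-randomised trial the treatment contrast varies between clusters, so its standard error has to come from variation between clusters. The model as written takes it from variation between persons. If parents and siblings change together, three members of a family carry less information than three unrelated people, and the standard error of the group-by-time effect comes out too small.

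In this trial, correlated change is what the intervention is meant to produce. Intervention families set collective goals and see each other's progress, and the Discussion builds its rationale on members influencing one another. Joint meals and joint activities feed directly into the eating and activity outcomes.

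The group-by-time test is also the decisive one, because Data Analysis looks at main effects only when the interaction is significant. The same model serves steps, moderate-to-vigorous activity, self-reported activity and fruit and vegetable intake in both trials. A test that runs above its nominal level could support claims of benefit that the number of families does not justify.

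**Working it through.** **Inputs**
- Unit of allocation: family (Randomization and Blinding).
- Unit of measurement: person (Study Design).
- 52 families, 3 members assumed per family, about 156 people, α = 0.05 (Participant Recruitment).
- ICC: not given. A range of 0 to 0.5 is assumed. The relevant quantity is the within-family ICC of *change*, given the covariates.

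**Step 1: the plan's own figure.** The article states no ICC, design effect or error rate. The nearest figure is the sample size, 52 × 3 = 156. ANCOVA power with f = 0.25, λ = f²N and denominator df = N − 2 − 4 gives N = 128 for numerator df 1. For numerator df 2 it gives N = 158 (power 0.797 at N = 156). The stated figure is therefore close to a variant that the article does not state. Another route also reaches it: 128 × 1.2 = 153.6, or 154 people, and 154 / 3 rounds up to 52 families. That would be a clustering allowance at ICC 0.1. The article does not show which route was used. Only the 52 families and the 3 members are carried forward.

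**Step 2: which error unit the model uses.** The label mixed-model could suggest a multilevel model. The Mauchly test, the epsilon corrections and the Levene test belong to the classical within-between ANCOVA, where mixed means one within-subjects and one between-subjects factor and the person is the error unit. No family factor is listed.

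**Step 3: size of the error.** For m members per family, the design effect is DE = 1 + (m − 1) × ICC. Treating members as independent shrinks the standard error by the factor 1/√DE. The actual two-sided size is 2 × (1 − Φ(1.96/√DE)). With m = 3:

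| ICC of change | DE | 1.96/√DE | Actual size | SE understated by (1 − 1/√DE) |
|---|---|---|---|---|
| 0 | 1.0 | 1.960 | 5.0% | 0% |
| 0.1 | 1.2 | 1.789 | 7.4% | 9% |
| 0.2 | 1.4 | 1.656 | 9.8% | 15% |
| 0.3 | 1.6 | 1.550 | 12.1% | 21% |
| 0.5 | 2.0 | 1.386 | 16.6% | 29% |

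All siblings are invited, so families may be larger than 3. With m = 4, the size runs from about 7% at ICC 0.05 to about 22% at ICC 0.5.

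**Step 4: check by simulation.** 20,000 null trials per ICC, 52 families of 3, T0-to-T1 change, no covariates:

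| ICC of change | t test on members | t test on family means |
|---|---|---|
| 0 | 0.050 | 0.050 |
| 0.1 | 0.074 | 0.051 |
| 0.2 | 0.093 | 0.047 |
| 0.3 | 0.123 | 0.052 |
| 0.5 | 0.168 | 0.050 |

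**Step 5: what a family term must capture.** Let member i of family j at time t have a family intercept u_j, a person intercept p_ij, a family-by-time effect v_jt and a residual e_ijt. The change from T0 to T1 is (v_j1 − v_j0) + (e_ij1 − e_ij0). Both intercepts cancel. The ICC of change is σ²_v / (σ²_v + σ²_e), so only v matters. A model that keeps T0 as an outcome and adds only family and person intercepts leaves the fault in place. Simulated with 52 families of 3 (400 runs per ICC), it rejected a true null in 5.75%, 11.5% and 17.25% of runs at ICC 0.1, 0.3 and 0.5. The Monte Carlo standard error, √(p(1 − p)/400), is about 1 to 2 percentage points, so these agree with Step 3.

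**The case against.** The strongest reply concerns size. The article gives no ICC, and at zero the test is exact. Stable differences between families cancel in change scores, so a high correlation of levels does not imply a high correlation of change. The family health climate covariate may absorb part of what is shared, and the simulation in Step 4 had no covariates. Steps, active minutes, questionnaires and diaries need not share one ICC, and nothing in the article supports 0.5 in particular. All of this stands. It limits how large the error can be said to be, but a covariate measured on the person is not a family error term.

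A second reply is that an article leaves detail to a statistical analysis plan. It does not help here, because the article itself fixes the factors, covariates, sphericity corrections, variance check, post hoc tests and software, and these do not match the unit of randomisation. A clustering allowance in the sample size, which cannot be excluded, would not correct the test either.

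A reader might infer three stronger points that the document does not support:
- **Every primary outcome's p-value is certainly too small.** That needs a positive ICC of change for each outcome, which is likely but not shown.
- **The planned confidence intervals are too narrow.** Data Analysis describes tests and post hoc comparisons and plans no intervals.
- **Anyone without a T2 questionnaire drops out of the T0-to-T1 comparison.** The article states no missing-data rule, so this would rest on software behaviour. It could not apply to accelerometer or diary outcomes, which stop at T1.

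**Conclusion.** The point holds in conditional form. The analysis as written ignores the unit of randomisation. Its group-by-time test exceeds 5% whenever members' changes are positively correlated within families, and the design makes that likely. For an assumed ICC of change between 0.1 and 0.5 and three members per family, the actual size lies between about 7% and 17%, and standard errors are understated by about 9% to 29%. These figures rest on the assumed ICC, equal families of three and, for the simulation, change scores without covariates. The direction of the error needs only a positive ICC of change. According to the Results section, SF2.0 data collection was ongoing and neither trial had been published, so the analysis wording should be corrected before the primary results are produced.

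**What to change.** In Data Analysis, put the family into the error structure of the treatment-effect test and keep the planned covariates.

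- **Outcomes at T0 and T1 only (accelerometer, diary):** a linear mixed model of the T1 value on group, the T0 value and the planned covariates, with a random intercept for family. There is one post-baseline occasion, so the model has no time or group-by-time term, and the group coefficient is the effect.
- **Questionnaire outcomes at T0, T1 and T2:** one of two forms.
  - Model T1 and T2 on group, time, group-by-time, the T0 value and the planned covariates, with a family random intercept and residual correlation within person. The group contrast at each visit is then the effect; the interaction alone would only compare T1 with T2.
  - Keep T0 as an outcome and add a family-by-time random effect. A family intercept alone is not enough (Step 5).
- Use Satterthwaite degrees of freedom, available in SPSS MIXED, and report the estimated ICC for each outcome.
- An analysis of family mean change is an acceptable alternative.

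The data and software stay the same. The cost is somewhat larger standard errors and p-values, and modest extra work because the two kinds of outcome need different models.

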### Participant Recruitment

Participants are recruited in schools, school holiday programs, music schools, and sports clubs via personal communication, newspapers, and email distribution lists of the Karlsruhe Institute of Technology. Power analyses for analysis of covariance with 2 groups and 4 covariates using G*Power [52] yields a total of 52 families with approximately N=156 participants (assuming 3 family members), to find a small-to-medium effect (α=.05, 1-β=.80, Cohen *f*=0.25). In order to increase power and to compensate for potential dropouts, we aim for a total of 60 families per trial. Please see Figure 3 for the planned participant flow for SF and SF2.0.

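### The Levene rule is reversed: Box-Cox is triggered when error variances look equal, and nothing is prescribed when they differ

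*Protocol article*

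**What the plan says.** All of the relevant text is in the Data Analysis section of the protocol article. The primary outcomes go into a "mixed-model analysis of covariance with time" as the within-subjects factor and group as the between-subjects factor. Before that, "all primary outcome data will be screened for normal distribution by using the Shapiro-Wilk test"; no transformation is attached to this step. The variance check comes later in the same paragraph: "homogeneity of the error variances will be checked, as assessed by Levene test". The next sentence gives the consequence: "If this test does not reveal significance, a Box-Cox transformation will be applied to the data".

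The section states no action for a significant Levene result and no significance level for the test. No other section of the article qualifies or corrects the rule.

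**The concern.** Levene's test takes equal variances as its null hypothesis, so a significant result is the warning sign. The plan attaches the transformation to the opposite result. Followed literally, outcomes with no sign of unequal variance are moved to a Box-Cox scale. Outcomes with demonstrated heterogeneity are left as they are, since no other remedy is named.

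The rule applies to the primary outcomes: steps, minutes of moderate-to-vigorous activity, self-reported activity, and fruit and vegetable intake. It decides the scale on which each is tested and reported. A Box-Cox scale with an estimated power has no natural unit, and the power would be estimated separately for each outcome and each trial. That sits awkwardly with the project's third question (Discussion, Overview), which asks whether effects are stronger in SF2.0 than in SF.

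A lesser point is that standard Box-Cox needs strictly positive data. Activity minutes and fruit and vegetable portions can be zero.

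**Working it through.** **Which test the rule refers to.** The sentence before the rule names only Levene's test, so the rule must mean that test. Reading it as the earlier Shapiro-Wilk screen would not rescue it. The null hypothesis there is normality, and a non-significant result again means no evidence of a problem.

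**Direction of the test.** For two arms, Levene's test forms z_ij = |y_ij − ȳ_i| and runs a one-way ANOVA on z. The null hypothesis is equal variance in the intervention and control arms.

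- Rule as written: apply Box-Cox if p ≥ α, so Pr(transform) = 1 − Pr(Levene rejects).
- Rule with the trigger turned round: apply Box-Cox if p < α, so Pr(transform) = Pr(Levene rejects).

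With equal variances, Levene rejects with probability close to α. The written rule therefore transforms with probability 1 − 0.05 = 0.95. As heterogeneity grows, the rejection probability rises towards 1 and the written rule's chance of transforming falls towards 0.

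**Inputs for a numerical illustration.**

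- α = 0.05. The Participant Recruitment section gives "α=.05, 1-β=.80, Cohen *f*=0.25" for the power analysis; the same level is assumed for Levene.
- Sample size. The same section says the calculation "yields a total of 52 families with approximately N=156 participants (assuming 3 family members"): 52 × 3 = 156, and 156 / 2 = 78 per arm if the arms are equal.
- Two other sizes. The target of 60 families gives 60 × 3 / 2 = 90 participants per arm, or 60 / 2 = 30 families per arm.
- SD ratios between arms of 1, 1.25, 1.5 and 2. These are assumed, because the article gives no SDs.

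The protocol has no figure of its own here to reproduce. The simulation used 4,000 runs per case, normal and independent observations, and mean-centred Levene. The Monte Carlo standard error is at most √(0.25 / 4000) ≈ 0.008.

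**Probability that Box-Cox is applied, rule as written:**

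| SD ratio | 78 per arm | 90 per arm | 30 per arm |
|---|---|---|---|
| 1 | 95% | 95% | 95% |
| 1.25 | 55% | 48% | 80% |
| 1.5 | 10% | 6% | 50% |
| 2 | 0% | 0% | 9% |

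The reversed trigger gives the complements. At 78 per arm these are about 5%, 45%, 90% and 100%. Median-centred Levene shows the same pattern (at 78 per arm, as written: 96%, 57%, 10% and 0%).

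In every column, transformation becomes less likely as the arms' variances diverge, which is the reverse of what the check is for.

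**The case against.** The strongest reply is that this is a slip of wording. The article says homogeneity is to be checked, the remedy is evidently meant for a failed check, and one word too many explains the sentence. That is likely. It does not make the published rule usable, and no other sentence shows which direction was meant.

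Second, leaving heterogeneous outcomes untransformed does limited harm to the error rate when arms are of similar size. Simulating a pooled-variance comparison of 78 versus 78 gave a type I error of 0.048, 0.049 and 0.052 at SD ratios of 1.3, 1.5 and 2. With 66 versus 90 at a ratio of 1.5, it was 0.037 when the larger arm was the more variable and 0.064 when the smaller arm was. Simple randomization of families can produce such imbalance, but the distortion is modest. This stands. The main cost of the written rule is needless transformation and loss of interpretability rather than a badly inflated error rate.

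Third, the percentages assume independent normal data, while participants are clustered in families and activity minutes and portions need not be normal. This also stands, so the figures are illustrative.

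Fourth, three related points are fair:

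- The article gives only the non-significant branch. That nothing is done after a significant result is an inference, though it is the plain reading.
- A correctly directed Levene rule could also put outcomes or trials on different scales, so that difficulty is not specific to the reversal. A standardized effect size would ease it in part.
- An offset for zeros is the kind of detail an article may leave to the analysis plan.

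None of these objections offers a reading under which the stated rule is right.

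**Conclusion.** The concern holds. As written, the rule transforms primary outcomes when Levene gives no sign of unequal variance and names no remedy when it does. This follows from the test's null hypothesis and depends on no assumed number.

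The size of the problem is how often the rule acts in the wrong place. With 78 per arm, it would transform about 95% of outcomes whose variances are equal, but only about 10% of those with an SD ratio of 1.5. These figures assume a Levene level of 0.05, equal arms, and normal, independent data.

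Whether a primary conclusion would change has not been shown, and with near-equal arms the type I error is little affected. The sentence should still be corrected before analysis because it fixes the scale of the primary results. Silently reading it the other way would be an undocumented departure from the published plan.

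**What to change.** **Minimum change.** Reword the sentence so that action is considered when Levene's test is significant, and state the level used. This costs one sentence. The article reports SF2.0 data acquisition as ongoing, so for that trial the correction can be dated before analysis. For SF, whose data collection has ended, it should be recorded as a correction to the published plan.

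**Preferable, but optional.** Drop the pre-test as a gate. Analyse each primary outcome on its original scale in both trials, with family-clustered robust standard errors or group-specific residual variances. Keep a transformation that allows zeros as a sensitivity analysis. This fixes the scale before the data are seen and keeps SF and SF2.0 results in the same units wherever the measure is the same. It needs a few lines of analysis text and no new data.

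### The planned Tukey post hoc tests do not fit the mixed, family-clustered design, and no pairwise comparison is the arm difference in change needed for the three-occasion self-report outcomes (minor)

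*Protocol article*

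**What the plan says.** The Data Analysis section of the protocol article plans a mixed-model ANCOVA. The two arms form the factor that varies between people. The repeated factor is described as "time (T_0_ and T_1_ for device-based physical activity; T_0_, T_1_, and T_2_ for self-reported physical activity and healthy eating) as within-subjects". That gives four group-by-time cells for accelerometer outcomes and six for self-report. After the Mauchly test, "results will be corrected accordingly (ε>0.75 Huynh-Feldt, ε<0.75 Greenhouse-Geisser"; this correction is described for the model results. The follow-up is then named: "Moreover, Tukey-corrected posthoc tests will be considered for detailed interpretation of results". A further rule concerns order: "Main effects will only be considered if the interaction is found to be significant". The section does not say which means the Tukey tests compare or which error term they use.

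Under Randomization and Blinding, "Both trials (SF and SF2.0) are cluster randomized controlled trials with 2 groups", the cluster being the family. The Overview in the Discussion sets the questions: whether activity and healthy eating rise relative to controls, and whether changes last after the intervention period. Self-reported activity and fruit and vegetable intake by questionnaire, measured at all three occasions, are listed among the primary outcomes.

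**The concern.** Tukey's method in its classical form covers all pairwise differences among independent means with a common standard error. None of the sets of means available here has that structure:

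- **Group alone:** two levels give one comparison, so there is no multiplicity to correct.
- **Time alone:** the means come from the same people and are correlated. The section itself allows for unequal covariances over time when it applies the epsilon correction to the model results, and it states nothing equivalent for the follow-up tests.
- **Group by time:** some pairs compare the same people at two occasions and others compare different people, and these have different standard errors.

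There is also a question of target, which does not depend on the error term. With three occasions the interaction has two degrees of freedom. A significant result does not say whether the arms diverge at T1, at T2 or at both. Locating the effect is the job of the follow-up tests, and a set of pairwise cell comparisons does not contain the contrast that does it.

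**Working it through.** **Inputs.** The plan gives no figure for the post hoc tests. The sample size (Participant Recruitment, "α=.05, 1-β=.80, Cohen *f*=0.25") serves only to set the scale: 52 families and about 156 people, so 26 families and 78 people per arm. A noncentral-F calculation with four covariates gives 158 with two numerator degrees of freedom, close to 156, and 128 with one. The point does not depend on this. The correlation ρ between occasions and the family intraclass correlation (ICC) are not in the article. They are assumed at 0.3 to 0.7 and at 0 or 0.2. Covariates are left out.

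**1. Which comparisons exist.** Six cells give 6 × 5 / 2 = 15 pairs: 3 between arms at the same occasion, 6 within an arm, and 6 that cross arm and time. The arm difference in change from T0 to T1 is (app T1 − app T0) − (control T1 − control T0). It has four non-zero coefficients, and a pairwise comparison has two. So none of the 15 is this contrast, and the same holds for T0 to T2. With two occasions the interaction has one degree of freedom and is itself this contrast.

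**2. Why one error term cannot serve all pairs.** With variance σ², n per arm and equal correlation ρ, a within-arm difference has variance 2σ²(1 − ρ)/n and a between-arm difference 2σ²/n. The standard errors differ by a factor 1/√(1 − ρ), which is 1.41 at ρ = 0.5. The Tukey critical value for six means, on the scale of a t statistic, is 2.87, a nominal per-pair level of 0.4%.

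- Within-person error used for a between-arm pair, ρ = 0.5: the effective cut-off is 2.87 × √0.5 = 2.03, so the size is 4.2%. At ρ = 0.7 it is 2.87 × √0.3 = 1.57, size 11.6%.
- Pooled cell error used for a within-arm pair, ρ = 0.5: the effective cut-off is 2.87 / √0.5 = 4.06, size 0.005%.

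**3. Family-wise error, no true effect, three occasions** (4,000 runs per row, 26 families of 3 per arm, nominal 5%):

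| ρ | Family ICC | One within-person error | One pooled cell error | Each contrast's own SE |
|---|---|---|---|---|
| 0.3 | 0 | 10.3% | 3.3% | 5.2% |
| 0.3 | 0.2 | 20.2% | 8.9% | 5.4% |
| 0.5 | 0 | 18.4% | 2.4% | 4.9% |
| 0.5 | 0.2 | 29.0% | 6.5% | 4.8% |
| 0.7 | 0 | 34.1% | 2.0% | 4.9% |
| 0.7 | 0.2 | 43.1% | 5.6% | 4.2% |

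The last column uses paired standard errors within an arm and family-level ones between arms, with the same Tukey critical value. Over all settings, including two occasions, it runs from 4.2% to 5.9%. In the pooled column the excess at ICC 0.2 comes from between-arm pairs that ignore the family; within-person pairs stay far too conservative.

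**4. Unequal correlations over time.** Take time alone, with correlations 0.8 (T0–T1), 0.5 and 0.5. On the scale of σ², the difference variances are 0.4, 1.0 and 1.0, average 0.8. The Tukey cut-off for three means is 2.36, nominal per-pair size about 1.8%. For T0–T1 the effective cut-off is 2.36 × √(0.8/0.4) = 3.34, size 0.1%. For T0–T2 it is 2.36 × √(0.8/1.0) = 2.11, size 3.5%. The simulated family-wise error stays near nominal, at 5.7% to 5.9%: the error is shared out wrongly more than it is inflated.

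**The case against.** The strongest reply is that the article never commits to a single error term or to all pairs of cells. Tukey-corrected can mean only that a Tukey critical value is applied to each contrast's own standard error, and the last column of the table shows that this works. The choice of error term is also something an article may leave to an analysis plan. Both arguments stand. A reader might infer from the Tukey sentence that the planned tests have wrong error rates; the document does not support that. The liberal and conservative figures are conditional on an implementation that the text leaves open.

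Three other strong readings also fail.

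- **False positives of 20% to 44%.** With 78 per arm, no clustering and ρ of 0.5 to 0.8, one within-person error gives about this rate. If the tests are run only after a significant interaction, the probability of any false declaration falls to 3% to 4%. The article states its interaction rule for main effects and leaves the order of the post hoc tests open.
- **A pooled error misses nearly every within-arm change.** With a true effect of 0.5 SD at T1 only and a significant interaction, it still finds the app arm's T0–T1 change in about 70% of runs.
- **The planned tests lack power because of the error term.** In that same setting the pooled error finds the T1 arm difference in 60% to 63% of runs, against 88% to 99.7% for a change contrast with Bonferroni over two. A between-person error is the right kind for that pair. The gap comes from correcting for 15 comparisons instead of two and from using baseline.

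It can also be said that, under randomization, the arm difference at T1 or T2 estimates the effect at that occasion. That is true, but it leaves chance baseline differences between about 26 families per arm uncorrected, and it is not the quantity that the interaction tests.

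Finally, the tests are optional and interpretive. The group-by-time interaction does not depend on them.

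**Conclusion.** The point holds as a minor one. The plan names a procedure whose classical assumptions do not match its own design. More importantly, the procedure does not deliver the contrasts that the three-occasion self-report outcomes need. This second part is a matter of counting coefficients and rests on no assumed value. The first part is conditional. With a single within-person error, family-wise error would be 10% to 43% in the settings tabulated. With a single pooled error, within-person pairs would have almost no chance of rejection under the null. With each contrast's own standard error, the level is held. These figures rest on assumed correlations and ICCs and omit the covariates. Nothing here shows that the interaction test is wrong or that the Tukey critical value is unusable. The accelerometer outcomes are not affected as to target, since their 1-df interaction is already the arm difference in change.

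**What to change.** Replace the Tukey sentence with planned contrasts, for example:

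> For outcomes measured at three occasions, follow-up consists of the arm differences in covariate-adjusted change from T0 to T1 and from T0 to T2. Each has its own model-based standard error, allowing for repeated measures and for clustering within families. P values are Holm-adjusted over the two contrasts within an outcome. Within-arm changes are reported descriptively.

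Two-occasion accelerometer outcomes need no such step.

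The cost is one or two sentences in the analysis plan and fewer pairwise p-values in the report. No new data are needed and the sample size does not change. The article describes SF2.0 data collection as ongoing, so on its account the change could be made before that trial's results are known.
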